## Abstract

Background

Foreign body airway obstructions (FBAOs, choking) are a significant cause of preventable mortality. Abdominal thrusts, back blows, and chest compressions are traditional interventions. However, suction-based airway clearance devices (ACDs) have recently been marketed as an alternative. Of note, there is limited published evidence regarding their efficacy and safety. Our research has two aims: (1) to investigate what situational and patient factors are frequently identified, and which are associated with relief of the FBAO and survival in individuals with FBAOs treated with an ACD; and (2) to describe the experience of individuals who have used ACDs in response to a FBAO and identify facilitators and barriers to the use of ACDs compared to traditional interventions.

Methods and analysis

A prospective database will be developed using an online reporting system to capture ACD uses, independent of manufacturers, from July 1st, 2021 to December 31st, 2023. Descriptive statistics will be used to summarize cases, outcomes, and adverse events. Clinically important subgroups will be stratified for analysis, including the severity of obstruction, patient demographics, and training of ACD users. Semi-structured interviews will also be conducted with a subset of ACD users to describe in detail their experience using the device. Themes from these interviews will be assessed using the theoretical domains framework.

Discussion

This study will improve the evidence surrounding ACDs and compare it to current data for traditional techniques, with the aim of optimizing FBAO treatment. Data on ACDs are urgently needed as these devices are already being used by parents, caregivers, lay rescuers, and healthcare professionals to respond to choking emergencies. This evaluation will provide important information about their effectiveness and any safety concerns which can inform the public, resuscitation guidelines, and future research studies.

## Introduction

Foreign body airway obstructions (FBAOs, choking) are preventable injuries with a considerable mortality burden globally [1-5]. The outcome of a FBAO is determined largely by bystander actions taken outside of the hospital setting, and yet there is a paucity of contemporary data informing the best response to be undertaken by lay rescuers and first responders [6].

The recent systematic review, authored by Couper et al., best summarizes the guiding literature in this area and highlights the limitations of current data [6]. Current recommendations from resuscitation councils, influenced by the International Liaison Committee on Resuscitation’s (ILCOR) Consensus on Science with Treatment Recommendations (CoSTR), suggest a combination of abdominal thrusts, back blows, and chest compressions as the core interventions for FBAO [7]. Notably, the majority of data are almost entirely case series, retrospective in nature, and no studies compare which intervention is superior in specific settings.

The limitations of this data reflect the challenges of conducting rigorous research in the field of resuscitation, especially in the pre-hospital environment. FBAOs are relatively rare events, and it is nearly impossible to conduct randomized studies where interventions are assigned as the vast majority are treated before emergency medical service (EMS) workers arrive [8]. Further, reliance on only healthcare records (either from EMS or physicians) may omit nuances in situational factors or interventions that researchers are trying to evaluate. Conversely, data acquired from the memory of the patient or bystanders are subject to recall bias and are likely influenced by poor medical literacy [9]. This makes the data collected more limited and of lower quality compared to other areas of medical research. It also blurs the standard that new interventions must meet before being deemed safe and, subsequently, effective.

One new FBAO intervention that has been described in the past decade is airway clearance devices (ACDs). These externally applied, non-powered, portable suction devices have been marketed as an alternative when traditional FBAO techniques fail and fall into two broad types, which, despite their similarities, have considerable differences in their design. Non-invasive ACDs are primarily manufactured by LifeVac© (LifeVac LLC, Nesconset, New York, USA), and consist of a facemask attached to a compressible bellows system [10]. Applying the mask to the choking person’s face creates a seal, followed by a rapid depression of the plunger system and a firm pull upwards. Minimally invasive ACDs are primarily manufactured by Dechoker© (Dechoker LLC, Concord, NC, USA), and consist of a short oropharyngeal tube that acts as a tongue depressor when the external face mask is applied [11]. The attached cylinder has a plunger that is pulled sharply to create the negative pressure system once a seal is formed with the mouth. Both contrast with other suction devices (e.g., Laerdal© V-Vac®) that do not have the external anchor of the face mask and can enter deeper into the oral airway [12]. Both devices offer training primarily through online videos from their websites, which can be viewed by purchasers and the public. 

However, two independent systematic reviews recently conducted concluded that there is insufficient evidence to support or discourage ACD use in the treatment of FBAO [6,13]. Both reviews only identified ten unique cases describing the safety of LifeVac’s ACD, all of which were successful at FBAO relief with no adverse events documented. They concluded with a recommendation that further evaluation in a research setting would be beneficial to determine the safety and effectiveness profile of ACDs.

Updated evidence in this area is required urgently. As sales of ACDs are increasing worldwide, the public and resuscitation councils require them to make informed decisions on their utility [10,11]. If the safety and effectiveness profile remain promising, then acknowledging ACDs as an alternative to traditional techniques is appropriate. If not, then this also needs to be clarified. Regardless, the first step in this process is to conduct research, independent of industry, examining these outcomes further.

This protocol details the present study’s proposed method to address the following objectives:

Research Aim One: To investigate what situational and patient factors are frequently identified, and which are associated with relief of the FBAO and survival in individuals with a FBAO treated with an ACD.

Research Aim Two: To describe the experiences of individuals who have used ACDs in response to a FBAO and identify facilitators and barriers to the use of ACDs compared to traditional interventions.

## Materials and methods

This is a multi-method, international observational study that will run from July 1st, 2021 to December 31st, 2023. Two research study designs will be used to address the research aims.

Study development

Following the publication of the systematic review on the effectiveness of ACDs in January 2020, the research team met in late 2020 to discuss a strategy for future investigation [13]. A draft protocol was created and underwent several revision cycles until a final version was completed and agreed upon. In early 2021, contact was made with each manufacturer to arrange a meeting where an overview of the proposed study was introduced and discussed. The CEO of each respective company, as well as several members of their administration and/or medical team, were in attendance, along with the research team. Following this, the project protocol was provided to each company to review before confirming their interest in participating. In March 2021, letters of support were signed by the CEOs of both companies, agreeing to participate to the extent that was outlined in the provided protocol, including assistance with the identification and recruitment of participants. The arms-length independence structure of the project, where manufacturers would not have any role in data collection, analysis, and reporting was reaffirmed. The study was then reviewed and approved by the Health Research Ethics Committee of the University of New South Wales (HC210242) on May 25, 2021.

Following ethics approval, a subsequent meeting was coordinated with each company with a similar cohort of representatives as the initial meeting. Here, the protocol was reaffirmed by the research team, and planning for the launch of the prospective component was discussed. A member of the research team was available to answer any questions the manufacturers had regarding the study during this period via email or phone.

Of note, no significant changes to the study protocol were made after the initial meeting with the manufacturers. A pre-print version of the a priori protocol was released on medRxiv while awaiting peer review [14].

Study one: prospective database development and evaluation

Participants and Recruitment Procedure

Participants who meet the following criteria will be eligible for inclusion in the study:

1. Individuals 18 years of age or older, who have used an ACD on a human to attempt to dislodge a FBAO. 

2. Individuals who are not cognitively impaired, with no intellectual disability or mental illness.

The only exclusion criteria outside of those not meeting the above will be anyone unwilling to provide consent or those who are non-English or Spanish-speaking (as the survey and interview guide will only be available in these languages).

ACD users will be invited to participate once they have been identified. Identification will occur in one of three methods. Both companies have agreed to include information on their webpage where users can learn about the research study and access a link to the data collection survey on an independent site if they wish to participate. Companies also agreed to notify potential participants who report ACD use to them directly via email, phone, or social media about the research study. A standardized e-mail was given to the companies to be sent to participants on behalf of the research team in this case. Finally, a website independent of all ACD manufacturers will be setup by the research team where interested individuals can learn more about the study and sign up to participate without the involvement of the manufacturers. It is believed that this will empower users who have had an unfavorable experience with ACDs to feel comfortable reporting without the stress of doing so directly to the manufacturers.

The initial electronic message sent to all interested parties will contain a link to the online survey where participants will have access to the participant information statement and consent form (PISCF) as well as the survey if they wish to proceed. At the end of the survey, participants will be able to indicate if they are interested in participating in an optional interview to help achieve Research Aim Two (see section below). 

Data Collection

Online surveys will be administered using digital survey software (Qualtrics, Provo, UT). The data collection tool was developed by the research team, and then beta-tested among ten individuals with no experience in healthcare or research. They were asked to provide feedback on the overall format of the tool as well as on any specific questions that were difficult to comprehend or were too complex to be answered in a survey format. Based on their comments, the survey was revised prior to being uploaded to the Qualtrics system.

Data will be collected in four domains: participant (ACD user), patient (choking person), situational, and outcome (Table 1). Furthermore, participants will be asked to make several agreement statements to further assess their experience.

**Table 1 TAB1:** Summary of collected variables via online survey. ACD: airway clearance device; CPR: cardiopulmonary resuscitation; EMS: emergency medical services; FBAO: foreign body airway obstruction.

Data category	Variables
Participant (ACD user)	Demographics, relationship to the person who choked, previous first aid or medical training, and previous experience with airway clearance devices (e.g., training, practice, or personal use)
Patient (choking person)	Demographics, medical comorbidities, functional status pre-FBAO, and FBAO history
Situational	Date and location of FBAO, foreign body details, witnessed status, severity of FBAO, patient status at time of intervention (e.g., consciousness, crying/speaking), FBAO intervention details, ACD intervention details, CPR intervention details, and EMS activation
Outcome	Relief of FBAO, survival, survival with good neurological function, functional status post-FBAO, and adverse events

Participants will be provided with an email contact for the research team in case they are unsure how to respond to a particular question and want clarification before submitting their response. Further, all participants will be asked to consent to receiving a follow-up email in the event the research team requires clarification of their responses to ensure accuracy of responses as well as confirmation that the event occurred. Once their responses are checked by one of the research team members for clarity and follow-up is conducted if needed, the results of the survey questions will be de-identified and assigned a unique study ID.

Study two: qualitative evaluation of ACD users’ experiences

Participants and Recruitment Procedure

Participants in this study will be a subset of the individuals who participated in study one (prospective evaluation). All participants after January 1st, 2022, will be invited to consent to an optional interview further discussing their experiences with ACDs. A six-month delay will occur to ensure the research design for the prospective study is functioning effectively before integrating the optional interviews.

Data Collection

Semi-structured interviews will be conducted using either online teleconferencing software or the telephone. This will also allow data collection to be ongoing while respecting regional COVID-19 social distancing restrictions. An interview guide will be employed to facilitate the session and ensure consistency between interviewers. Interviews will be conducted by research team members trained on the interview guide. Each interviewer will have a rehearsal session with a simulated participant monitored by the primary investigator. Subsequently, they will all have their initial and randomly selected interviews monitored by another investigator to ensure a safe and high-quality experience for all involved. The interviews will be audio-recorded and then subsequently transcribed by the researchers using transcription software.

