As a sampling method, self-reporting has well-known limitations. It skews results toward extremes of outcomes (e.g., success or death) [9]. It also relies on non-medically trained personnel to report situational and outcome details, which may be prone to recall bias [9]. To address the first limitation, we acknowledge that this study will not result in the ability to say that ACDs have a certain percent effectiveness. Instead, this initial work will present evidence as to whether or not ACDs have the potential to be effective and safe. If positive, this data may support the implementation of ACDs in a small centre or organization to formally study the intervention in a more rigorous environment. To address the second limitation, all submissions will have a medical professional review the results prior to de-identification, and participants will be contacted if the data is inconsistent or seems medically inaccurate.

Despite its limitations, self-reporting as a sampling strategy is not new in this field of research. Redding published a case series of 225 FBAOs that were compiled by the American Heart Association through a self-reporting method [21]. This paper makes the largest single contribution to the evidence summarized in Table 2, and to ILCOR's CoSTR for FBAO interventions [6,7].

The greatest strength of this study is that it will produce the first data on ACDs that will be collected and analyzed independently of industry. Following a protocol published a priori with clearly defined outcomes and a publicly available reporting system, we aim to provide the public with information in as unbiased fashion as possible at present. In a field devoid of evidence, the first step to improving knowledge is to create a base on which to build future studies and further evaluations.

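### Reporters with a commercial tie to a device manufacturer are eligible and not visibly identified, so independence of the outcome source is not assured

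*Protocol article*

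**What the plan says.** Under Materials and methods, Study one, Participants and Recruitment Procedure, there are two inclusion criteria: "Individuals 18 years of age or older, who have used an ACD on a human to attempt to dislodge a FBAO" and "Individuals who are not cognitively impaired, with no intellectual disability or mental illness". The exclusions are then closed: "The only exclusion criteria outside of those not meeting the above will be anyone unwilling to provide consent", together with people who speak neither of the two survey languages. Ties to a manufacturer are not mentioned.

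Independence from industry is stated in three places:

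- The Abstract describes a database "using an online reporting system to capture ACD uses, independent of manufacturers".
- Study development says that "manufacturers would not have any role in data collection, analysis, and reporting".
- The Discussion names as the greatest strength that "it will produce the first data on ACDs that will be collected and analyzed independently of industry".

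Study development also discloses that the companies agreed to take part, "including assistance with the identification and recruitment of participants".

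**The concern.** Relief, survival, adverse events and the answers from which the cerebral performance category is assigned all come from the person who used the device. The investigators classify outcomes from that account; the article describes no second source such as a health record. A reporter who works for, sells for or is paid by a manufacturer would be a source of outcome data with a commercial interest, however independent the survey site and the analysts are.

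The protocol accepts that manufacturer involvement can influence reporting. It sets up its own website partly so that users with a bad experience can report without going through a company. No matching safeguard is shown against interested favourable reports.

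At stake are the summary of relief and adverse events, the comparison by device type, and how far a reader can rely on the independence statement. This is a separate matter from company help with recruitment, which is openly stated.

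**Working it through.** The article states no sample size, expected failure count or share of affiliated reporters, so there is no figure of its own to reproduce. The main check is a comparison of sections.

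**1. Who may report.** The criteria cover age, device use on a human, cognitive and mental health, consent and language. A manufacturer's employee, distributor, trainer or paid promoter can satisfy all of them.

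**2. What is recorded about the reporter.** The participant row of Table 1 lists demographics, relationship to the patient, first aid or medical training, and experience with ACDs. No tie to a company is listed. The table is a summary.

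**3. How results are split.** The stratified analysis (Results, Study one) uses age group, severity, neurological impairment, device type, user training, and single or multiple interventions. Affiliation is not among them.

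**4. What is checked.**
- Data Collection: clarity of the answers and confirmation that the event took place.
- Results: assignment of outcomes, with a second check by a physician.
- Discussion: consistency and medical plausibility.

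A coherent report from an affiliated user passes all of these.

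**5. What independence covers.** Study development defines it by who collects, analyses and reports. The survey is on an independent site, the research team built it, and the team assigns outcomes. None of the three statements claims that reporters have no industry ties.

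**Illustration of size (all inputs assumed).** Let p be the relief proportion among independent reports and f the share of affiliated reports, all of them relieved with no adverse event. Pooled relief is (1 − f)p + f, so the shift is f(1 − p). Any adverse-event proportion is multiplied by (1 − f).

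| Assumption | Independent reports | All reports | Shift |
|---|---|---|---|
| f = 10% (5 of 50) | 36/45 = 80% | 41/50 = 82% | 0.10 × 0.20 = 2 points |
| f = 20% (10 of 50) | 32/40 = 80% | 42/50 = 84% | 0.20 × 0.20 = 4 points |

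If the 5 affiliated reports in the first row all concern one of two devices, with independent reports at 18/22 = 81.8% and 18/23 = 78.3%, the first becomes 23/27 = 85.2%. The difference between devices goes from 3.6 to 6.9 points.

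For scale, the 95% Wilson interval for 36/45 is about 66% to 89%. The assumed shifts are small beside that sampling error.

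**The case against.** A reader might infer that the claimed main strength is false as written. The documents do not support that. Independence is defined by who runs the study, and those tasks are assigned to the research team. Eligibility of affiliated users allows an industry source; it does not show that one will report, and nothing in the article says that one is expected. This part of the objection stands.

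A reader might also infer that affiliated reports could never be removed once pooled. That does not follow either. Data management and privacy says that a code linking study ID to participant is kept, and participants are asked to agree to a follow-up e-mail. The stated purpose of that contact is clarification and confirmation of the event, but a route back to the reporter exists. What can be said is that the listed variables would not identify these reports.

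Table 1 is a summary and the survey is not shown, so the question may already be asked. That also stands, and makes the recommendation conditional. It does not change the eligibility rule, which the article states in full and closes.

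Finally, the effect is hypothetical and modest, and the Discussion says that the study will not yield a percent effectiveness and that self-reporting skews results. This limits the weight of the point without removing it. The study still means to judge whether the devices have the potential to be effective and safe, and it still compares device types.

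**Conclusion.** The point holds in a limited form. The closed eligibility rule admits reporters with a commercial tie to a manufacturer, and nothing shown in the article would visibly identify them. Independent collection, handling and analysis are secured. Independence of the people who supply the outcomes is not, and the claim to be "the first data on ACDs that will be collected and analyzed independently of industry" can be read as promising it.

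The size of any bias cannot be derived from the document. The shift of 2 to 4 points in relief rests on an assumed affiliated share of 10% to 20%, an assumed 80% relief among other reporters, 50 reports in all, and relief in every affiliated report. The article does not say that reports, or failures, will be few, so no larger effect should be argued on that ground. This is a cheap improvement against a plausible source bias, not a failure of the design.

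**What to change.** Unless the full survey already contains it, add one item asking whether the reporter has, or has had, employment, distribution, sales commission, paid promotion or other material benefit from any ACD company. Then:

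- keep these reports in the database and state their number;
- report relief, survival, adverse events and the device-type contrast with and without them;
- carry the answer into Study two as a descriptor of the interviewees, who are a subset of Study one.

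Excluding affiliated reporters from the main analysis is not needed. It would discard genuine device uses, including any failures that they report, and is a debatable trade-off.

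If the item is not added, limit the strength statement in the Discussion to independent collection, handling and analysis of the data.

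The cost is one extra survey question, a minor ethics notification and a small sensitivity analysis.
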